## Abstract

**Background:**

Urinary and (peripheral and central) intravenous catheters are widely used in hospitalized patients. However, up to 56% of the catheters do not have an appropriate indication and some serious complications with the use of these catheters can occur. The main objective of our quality improvement project is to reduce the use of catheters without an appropriate indication by 25–50%, and to evaluate the affecting factors of our de-implementation strategy.

**Methods:**

In a multicenter, prospective interrupted time series analysis, several interventions to avoid inappropriate use of catheters will be conducted in seven hospitals in the Netherlands. Firstly, we will define a list of appropriate indications for urinary and (peripheral and central) intravenous catheters, which will restrict the use of catheters and urge catheter removal when the indication is no longer appropriate. Secondly, after the baseline measurements, the intervention will take place, which consists of a kick-off meeting, including a competitive feedback report of the baseline measurements, and education of healthcare workers and patients. Additional strategies based on the baseline data and local conditions are optional. The primary endpoint is the percentage of catheters with an inappropriate indication on the day of data collection before and after the de-implementation strategy. Secondary endpoints are catheter-related infections or other complications, catheter re-insertion rate, length of hospital (and ICU) stay and mortality. In addition, the cost-effectiveness of the de-implementation strategy will be calculated.

**Discussion:**

This study aims to reduce the use of urinary and intravenous catheters with an inappropriate indication, and as a result reduce the catheter-related complications. If (cost-) effective it provides a tool for a nationwide approach to reduce catheter-related infections and other complications.

**Trial registration:**

Dutch trial registry: NTR6015. Registered 9 August 2016.

## Background

Healthcare-associated infections (HAIs) are associated with an increased mortality, a longer duration of hospital stay, which results into an increase in substantial costs. The use of invasive medical devices (e.g., urinary catheters, peripheral intravenous catheters (PIVCs) and central venous catheters (CVCs)) are important risk factors for the development of HAIs, which have prevalence of 7.1% measured in a combined point prevalence survey in Europe [1]. So an efficient way to reduce HAIs is to avoid insertion of catheters without an appropriate indication and to reduce the number of catheter days.

In general hospitals 15–25% of patients have an indwelling urinary catheter during their hospital stay. Urinary tract infections are accountable for 40% of all nosocomial infections in Western world hospitals, and 71–80% of these patients had a urinary catheter [2–4]. Nevertheless, the incidence of unwarranted placement of urinary catheters in hospitalized patients is 14–65% [5–10].

PIVCs are the most frequently used invasive medical devices in hospitalized patients. However, 25–56% of the PIVCs inserted in the Emergency Department are inappropriate or even unused [11–16]. In a recent study of internal medicine departments in Spain 81.9% of the patients had one or more PIVCs, of which 19% were no longer necessary [17]. A PIVC can cause serious adverse events, with an incidence rate of catheter-associated bloodstream infection of 0.1% (0.5 per 1000 catheter days) [18].

Central line-associated bloodstream infections (CLABSIs) are a major problem in intensive care units (ICUs). A meta-analysis shows that implementation of central line bundles to reduce the incidence of CLABSIs are effective and cost saving in ICUs [19].

### Intervention studies to prevent catheter-related infections

Previous research suggests that multiple and well-organized interventions could reduce the number of HAIs. In a pilot study in our university hospital in the Netherlands 89.2% of the initial indications for urinary catheter use were appropriate. However, after 2–3 days the initial indication was mostly no longer present, resulting into an inappropriate indication, but not to a removal of the catheter. After education and daily assessment of the indication of urinary catheters, the duration of catheterization reduced from 1009 to 672 days in 149 patients (pre-intervention *n* = 74, post-intervention *n* = 75), and the number of catheter-associated urinary tract infections (CAUTI) decreased from 4 to 0 infections per 1000 catheter days (*p* = 0.04). Thereby the median length of hospital stay reduced from 13 to 9 days [20]. Very recently, a national program (dissemination of information to sponsor organizations and hospitals, data collection, and guidance on key technical and socioadaptive factors) in 603 US hospitals reduced CAUTI rates by 22% in non-ICUs [21].

Only a few studies evaluated the effect of interventions to improve the appropriate use of PIVCs. In 1994 a quality improvement project in the internal medicine wards of Minnesota reduced inappropriate use of PIVCs by 63% (43% vs 27%) [22]. Education and feedback to improve PIVC care significantly reduced the PIVC-associated bloodstream infections from 2.2 to 0.44 per 10.000 patients days in 10 non-ICUs [23]. Furthermore, in a general hospital in Spain the use of unnecessary peripheral and central venous lines decreased from 22.9 to 7.1% after a 1-year training program [24].

A multifaceted ‘bundle’ approach (education, hospital protocol, national program, and checklist intervention) to control CVC-associated bloodstream infection in an internal medicine department in Spain showed a decrease of 63.1% (14.1 to 5.2 per 1000 catheter days) [25].

Prevention of HAIs is an important part of the todays medical practice. However, the risks of the use of urinary catheters and mainly PIVCs are widely underestimated, and in the Netherlands no nationwide program to reduce the catheter-related infections is present.

## Methods and Design

### Objectives

In this de-implementation study we aim for a 25–50% reduction of the number of urinary and (peripheral and central) intravenous catheters without an appropriate indication, which will lead to a reduction of the number of catheter days and catheter-related complications.

### Study design and setting

The study design is a multicenter, prospective interrupted time series (Fig. 1), which will take place in seven hospitals in the Netherlands (three university and four general hospitals). We aim to reduce 25–50% of the catheters without an appropriate indication by a de-implementation strategy of multiple interventions. The clinical data collection will be once per 14 days during 8 months in both the pre- and post-intervention period. During these measurement days all patients with a urinary and/or (peripheral and/or central) intravenous catheter inserted during the hospital stay will be enrolled. The de-implementation strategies will start during a transition period of 4 months, while no patients will be included.

**Fig. 1 Fig1:**
[figure not shown]
Interrupted time series for appropriate use of catheters

### Appropriate use of catheters

We defined a list of valid indications for urinary and intravenous catheter placement, based on the literature (Table 1) [26–29]. All other indications are defined as inappropriate.

**Table 1 Tab1:** List of appropriate indications

Urinary catheter	Peripheral intravenous catheter	Central intravenous catheter
Acute urinary retention or bladder outlet obstruction (≥150 cc)	Delivery of peripherally compatible infusate (IV fluids and medications), at least once in 24 h	Delivery of non-peripherally compatible infusate (e.g., irritants or vesicants), regardless of proposed duration of use
Accurate measurements of urinary output in critically ill patients required for treatment	Transfusion of blood and blood products	PICC : delivery of peripherally compatible infusate, with a duration of use which will likely confine ≥ 6 days^b^
Volume measurements of urine output aim for diagnostics (24 h urine), which cannot be assessed by other collection strategies	Injection of contrast fluids	Invasive hemodynamic monitoring or requirement to obtain central venous access in critically ill patients -Nontunneled CVC : duration of use will likely confine < 15 days -PICC : duration of use will likely confine ≥ 15 days
Assist in healing of open sacral or perineal wounds in patients with urinary incontinence	Intravenous access for cardiac dysrhythmia	PICC : Delivery of cyclical or episodic chemotherapy that can be administered through a peripheral vein, provided that the proposed duration of such treatment is ≥3 months
Continuous bladder irrigation for hematuria	PIVC : duration of use will likely confine ≤ 5 days	Frequent phlebotomy (every 8 h), provided that the proposed duration of such use is ≥6 days
Patient requires prolonged immobilization	Midline : duration of use will likely confine ≤ 14 days^a^	PICC : Intermittent infusions or infrequent phlebotomy in patients with poor/difficult peripheral venous access, provided that the proposed duration of such use is ≥ 6 days
Palliative care for terminally ill if needed		PICC: For infusions or palliative treatment during end-of-life care
Pre- or postoperative according (local) protocol		Tunneled catheter or port : preferred if proposed duration is ≥ 31 day

^a^Use of PIVCs is preferred over use of midlines for infusion of peripherally compatible infusates up to 5 days

^b^Use of PIVCs or midlines is preferred over use of PICCs for infusion of peripherally compatible infusates up to 14 days

### Definition of catheter-related infections

We will use the definitions by Centre for Disease Control’s (CDC) National Healthcare Safety Network for catheter-related infection (Table 2) [30]. Thereby we will use probable definitions based on the CDC and the Dutch surveillance system ‘Prevention of Nosocomial Infections through Surveillance’ (Table 3) [31].

**Table 2 Tab2:** Definition of catheter-related infections [30]

Catheter-related infection	Definition
Healthcare-associated infection (HAI)	Infection where the date of event occurs on or after the 3rd calendar day of admission to an inpatient location, where calendar day 1 is the day of admission
Laboratory-confirmed bloodstream infection (LCBI)	Criterion 1: Patient has a recognized pathogen identified from one or more blood specimens by a culture or non-culture based microbiologic testing method which is performed for purposes of clinical diagnosis or treatment AND organism(s) identified in blood is not related to an infection at another site Criterion 2: Patient has at least one of the following signs or symptoms: fever >38.0 °C, chills, or hypotension AND organism(s) identified from blood is not related to an infection at another site AND the same common commensal (i.e., diphtheroids [Corynebacterium spp. not C. diphtheriae], Bacillus spp. [not B. anthracis], Propionibacterium spp., coagulase-negative staphylococci [including S. epidermidis], viridans group streptococci, Aerococcus spp., and Micrococcus spp.) is identified from two or more blood specimens drawn on separate occasions
Central line	An intravascular catheter that terminates at or close to the heart or in one of the great vessels (aorta, pulmonary artery, superior vena cava, inferior vena cava, brachiocephalic veins, internal jugular veins, subclavian veins, external iliac veins, common iliac veins, femoral veins) which is used for infusion, withdrawal of blood, or hemodynamic monitoring
Central line-associated BSI (CLABSI)	A LCBI where the central line was in place for >2 calendar days on the date of event, with day of device placement being Day 1, AND the central line was also in place on the date of event or the day before
Arterial or venous infection (VASC)	It must meet at least one of the following criteria: 1. Patient has organisms from extracted arteries or veins identified by a culture or non-culture based microbiologic testing method which is performed for purposes of clinical diagnosis or treatment. 2. Patient has evidence of arterial or venous infection on gross anatomic or histopathologic exam. 3. Patient has at least one of the following signs or symptoms: fever (>38.0 °C), pain, erythema, or heat at involved vascular site AND more than 15 colonies cultured from intravascular cannula tip using semiquantitative culture method. 4. Patient has purulent drainage at involved vascular site.
Urinary tract infection (UTI)	Patient has at least one of the following signs or symptoms: fever >38.0 °C, suprapubic tenderness, costovertebral angle pain or tenderness, urinary urgency, urinary frequency, dysuria^a^ AND urine culture with no more than two species of organisms identified, at least one of which is a bacterium of ≥10^5^ CFU/ml
Indwelling catheter (Foley catheter)	A drainage tube that is inserted into the urinary bladder through the urethra, is left in place, and is connected to a drainage bag.
Catheter-associated UTI (CAUTI)	A UTI where an indwelling urinary catheter was in place for >2 calendar days on the date of event, with day of device placement being Day 1, AND an indwelling urinary catheter was in place on the date of event or the day before

^a^An indwelling urinary catheter in place could cause patient complaints of frequency, urgency, or dysuria, and therefore these cannot be used as symptoms when catheter is in place

**Table 3 Tab3:** Probable definition of catheter-related infections [31]

Catheter-related infection	Definition
Probable laboratory-confirmed bloodstream infection (LCBI)	Patient has at least one of the following signs or symptoms: fever >38.0 °C, chills, or hypotension AND organism(s) identified from (peripheral) blood or catheter segment is not related to an infection at another site AND defervescence within 48 h of catheter removal or initiation of appropriate antibiotic therapy
Probable central line-associated BSI (CLABSI)	A probable LCBI where the central line was in place for >2 calendar days on the date of event, with day of device placement being Day 1, AND the central line was also in place on the date of event or the day before
Phlebitis	Local pain, warmth, tenderness, erythema, and a palpable cord along the vein OR by positive sonographic examination in conjunction with erythema and edema of the extremity
Probable urinary tract infection (UTI)	Patient has at least two of the following signs or symptoms: fever >38.0 °C, suprapubic tenderness, costovertebral angle pain or tenderness, urinary urgency, urinary frequency, dysuria^a^ AND positive nitrite or leukocyte esterase dipstick test OR pyuria (>10 leukocytes/mm^3^) OR organism(s) seen in gram straining in not centrifuged urine OR two sequential urine culture (≥10^2^ CFU/ml) with the same uropathogens (gram negative bacteria or S. saprophyticus) OR urine culture with one species of organism identified (≤10^5^ CFU/ml) in a patient treated with appropriate antibiotic therapy OR the diagnose ‘urinary tract infection’ by doctor OR doctor starts appropriate antibiotic therapy
Probable catheter-associated UTI (CAUTI)	A probable UTI where an indwelling urinary catheter was in place on the date of event or the 7 days before

^a^An indwelling urinary catheter in place could cause patient complaints of frequency, urgency, or dysuria, and therefore these cannot be used as symptoms when catheter is in place

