### Primary and secondary endpoints

The primary endpoint is the percentage of patients with an inappropriate indication for urinary and intravenous catheter on the days of data collection. Secondary endpoints are catheter-related infections and other complications, catheter reinsertion rate, use of antibiotics, length of hospital stay (and ICU) in days, in hospital mortality, and costs of the de-implementation strategy and the main healthcare costs.

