### Assessments

The presence and indications for the catheter use will be extracted from the medical records in combination with observations of the admitted patients. During the day of measurement the indication of the urinary and/or intravenous catheter and some patient variables will be collected. If there is an unclear indication of a catheter, the investigator will contact one of the healthcare workers (HCWs) to verify this information.

After discharge, the occurrence of catheter-related infections (see Table 3 for definitions) [31], with diagnostics and treatment, or other catheter-related complications (measured in registry and by investigator), the number of catheter days, reinsertion rate, use of alternatives for an indwelling urinary catheter (continence garments, condom catheters, intermittent straight catheterization), reason for admission, Charlson comorbidity index [32], duration of hospital (and ICU) stay, readmission within 30 days after discharge, and mortality (in hospital or within 30 days after discharge) will be collected from (electronic) medical- and nursing records. Furthermore, the nurse-to-patient ratios and the clinical work experience of residents will be collected.

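### The UTI part of the infection endpoint is counted in a window tied to catheter time, which the strategy shortens, so a fall in counted infections may be partly re-attribution

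*Protocol article*

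**What the plan says.** Under Primary and secondary endpoints, the article states: "Secondary endpoints are catheter-related infections and other complications, catheter reinsertion rate, use of antibiotics". Stay, mortality and costs follow. No endpoint counts UTIs irrespective of catheter status.

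Two attribution rules are given under Definition of catheter-related infections, and that section says both tables will be used:

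- **Table 2 (CAUTI):** "A UTI where an indwelling urinary catheter was in place for >2 calendar days on the date of event", and in addition "an indwelling urinary catheter was in place on the date of event or the day before". The window runs from catheter day 3 to the day after removal.
- **Table 3 (probable CAUTI):** "A probable UTI where an indwelling urinary catheter was in place on the date of event or the 7 days before". There is no minimum dwell, and the window closes 7 days after removal.

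The Assessments section refers to the second set when it describes collection after discharge: "the occurrence of catheter-related infections (see Table 3 for definitions"). It also records "use of alternatives for an indwelling urinary catheter (continence garments, condom catheters, intermittent straight catheterization").

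Table 2 separately defines a healthcare-associated infection (onset on or after calendar day 3 of admission) and a UTI, neither with a device condition. Neither is named as an endpoint. The Objectives expect fewer catheter days, and the Economic evaluation uses catheter-related complications as an input.

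**The concern.** The counting rule is worded identically before and after the intervention, but the length of its window is set by dwell time, which the strategy is meant to change. Take a patient whose catheter comes out earlier, or who is moved to intermittent or condom drainage, and who stays in hospital. A UTI late in that stay may fall outside the window in the post-intervention period. In the baseline period the same patient might still have been catheterised, and the UTI would have counted.

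The catheter-associated count alone therefore cannot separate a UTI that was prevented from one that is no longer attributed. UTIs under a replacement method, a possible harm of the strategy, are seen only if they happen to fall inside the indwelling-catheter window. This matters because preventing healthcare-associated infection is the rationale given in the Background, and because catheter-related complications enter the economic evaluation.

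**Working it through.** The article states no figure for this effect, so there is none to reproduce. The check is window arithmetic.

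**Inputs.** The pilot reports that "the duration of catheterization reduced from 1009 to 672 days in 149 patients", with 74 patients before and 75 after. Reading these as total catheter days per group (an assumption):

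- before: 1009/74 = 13.64 days per patient
- after: 672/75 = 8.96 days per patient, a change of −34%

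**Window lengths for L catheter days.** Table 2: day 3 to day L+1, which is L − 1 days. Table 3: day 1 to day L+7, which is L + 7 days.

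**Step 1: extreme bound.** Assume a constant daily UTI hazard that removal does not change, so that no UTI is prevented, and an unchanged stay long enough to contain the window.

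| Rule | Window before | Window after | Ratio per patient | Fall |
|---|---|---|---|---|
| Table 2 | 12.64 | 7.96 | 0.63 | 37% |
| Table 3, whole tail observed | 20.64 | 15.96 | 0.77 | 23% |
| Table 3, stay ends by day 16 | 16 | 15.96 | about 1.00 | about 0% |

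If dwell fell by only 10% or 25%, the Table 2 bound would be 1.36/12.64 = 10.8% or 3.41/12.64 = 27.0%. With assumed stays of 9 to 20 days and dwell going from 6 to 4, 8 to 5 or 10 to 7 days, the ratio is 0.57–0.67 under Table 2 and 0.80–1.00 under Table 3.

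**Step 2: a lower hazard off-catheter.** The Background says "Urinary tract infections are accountable for 40% of all nosocomial infections in Western world hospitals, and 71–80% of these patients had a urinary catheter", and that 15–25% of patients in general hospitals have an indwelling catheter. The implied crude odds ratio runs from (0.71/0.29)/(0.25/0.75) = 7.3 to (0.80/0.20)/(0.15/0.85) = 22.7. These are patient-level, confounded figures, used here only for illustration. Let the off-catheter hazard be 1/r of the on-catheter hazard. Under Table 2 the lost window is 12.64 − 7.96 = 4.68 days. The true fall in UTIs over the original 12.64 days is then 1 − (7.96 + 4.68/r)/12.64:

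- r = 7.3: 32.0%
- r = 22.7: 35.4%

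The counted fall is 37.0% in both cases, so the artefact is 37.0 − 32.0 = 5.0 or 37.0 − 35.4 = 1.6 points, that is about 2–5 percentage points.

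**Step 3: stay shortening in parallel.** In the pilot the median stay fell from 13 to 9 days, close to mean dwell in both periods (means against medians, so approximate). In the limiting case of a catheter in place from admission to discharge, the Table 2 window and the healthcare-associated window both run from day 3 to discharge. No in-hospital UTI is then left out, and the artefact is nil.

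**Step 4: per catheter-day.** Under the Step 1 assumptions:

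- Table 2: (7.96/8.96)/(12.64/13.64) = 0.96
- Table 3: (15.96/8.96)/(20.64/13.64) = 1.18

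The distortion is slight in one case and reversed in the other.

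**The case against.** The strongest counter-case is about size:

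- **Which table.** Table 3 is the set cited for ascertainment. Its 7-day tail catches many UTIs after removal, and in short stays it removes the artefact.
- **Hazard.** An unchanged hazard after removal contradicts the article's own Background, where catheterised patients carry most UTIs.
- **Stay.** The pilot's stay fell alongside dwell, leaving little time in hospital outside the window.
- **Denominator.** The Statistical analysis section names a rate ratio. The pilot reports infections per 1000 catheter days, and on that scale there is almost no spurious fall. The denominator may be fixed in an analysis plan that is not shown.
- **Symptoms.** Urgency, frequency and dysuria count only once the catheter is out, which raises ascertainment after removal.
- **Scope.** The endpoint is labelled catheter-related and is secondary. Antibiotic use, stay and mortality do not depend on the device.

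All of this stands as a limit on magnitude. None of it removes the mechanism: both windows follow dwell, no denominator frees them from it, and the device-independent outcomes are indirect and not specific to UTI.

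A reader might also infer from the Background that 20–29% of UTIs will escape the rule, as the complement of 71–80%. The documents do not support that. The figure describes nosocomial UTI patients in general, whereas this study enrols patients who have a urinary or intravenous catheter on a measurement day.

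**Conclusion.** The point holds as a limitation of one secondary endpoint. Counted catheter-associated UTIs per patient or per patient-day can fall partly through re-attribution, and the listed endpoints cannot show how much.

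A reader might go further and infer that a fall of about a third in these infections would be pure relabelling. The documents do not support that. The 37% figure requires Table 2, an unchanged stay and a hazard that removal leaves untouched. Under Table 3 the same bound is 0–23%. With an off-catheter hazard 7 to 23 times lower, the Table 2 artefact is about 2–5 percentage points, and it shrinks further if stay shortens in parallel.

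All sizes assume one continuous catheterisation per patient and the pilot's mean dwell. They show what the rule can produce and are not forecasts. The primary endpoint is unaffected.

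**What to change.** Keep CAUTI and probable CAUTI as defined. Add a supplementary secondary outcome, also used as a sensitivity input to the economic evaluation:

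- all healthcare-associated UTIs in enrolled patients, using the Table 2 UTI criteria with onset on or after calendar day 3 of admission
- counted whatever the device in place, per patient-day from the survey day to discharge
- tabulated by device at onset (indwelling, intermittent or condom, none), using the information on alternatives already collected

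The cost is wording and a modest amount of extra classification, since the records are already reviewed after discharge. The apparent effect on infection will probably be smaller, because UTIs unrelated to a catheter dilute it.

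The addition does not reach patients who are never enrolled because a catheter was avoided, or removed before the survey day, and who have no other qualifying catheter. State this as a limitation.

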### De-implementation strategy

We will use a bundle of interventions (Table 4), since it is known that multiple and well-organized interventions result into better improvements. The main intervention is the dissemination of the list of appropriate indications (Table 1), which will restrict the insertion of urinary and intravenous catheters by physicians and nurses. The recommendation will be to remove the catheters without or with an expired valid indication. A local ‘champion’ (one of the leading physicians) will be appointed to be responsible for the interventions in his or her department. The intervention period will start with a kick-off meeting, where a list of baseline data of the intervention hospital in comparison with the other study hospitals will be presented as a competitive feedback report [33]. If desired, feedback reports per department could be sent by e-mail to local investigators. Thereby two educational meetings about insertion, care and maintenance of urinary and intravenous catheters will be applied to change HCWs behavior. Furthermore, HCWs will be encouraged and reminded to remove inappropriate catheters by posters, pocket cards and e-mail messages. In addition to other studies, patients will be actively supported by education material to participate in their treatment.

**Table 4 Tab4:** De-implementation strategy

Interventions of de-implementation strategy
List of appropriate indications
Local ‘champion’
Kick-off meeting, including competitive feedback report of baseline data
Education meeting for healthcare workers
Education materials (e.g., posters, pocket cards)
Patient education materials
Optional interventions based on baseline data and local conditions per hospital

Subsequently, all impeded and promoted factors of this de-implementation strategy for both HCWs and patients will be evaluated by direct observations and interviews. Additional prevention strategies could be applied based on these affecting factors and local conditions in the different hospitals.

If this de-implementation strategy prove to be effective, persistent awareness of the local ‘champion’ in combination with recurrent surveillance of the appropriate use of catheters and catheter-related infections will improve the sustainability. Thereby the de-implementation rule “No indication = Remove catheter” will be recommended in national guidelines and local protocols.

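### A doctor's UTI diagnosis or antibiotic start can replace all laboratory evidence in the probable UTI and CAUTI definitions, so this uncontrolled secondary infection comparison could shift with labelling habits

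*Protocol article*

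**What the plan says.** The section on the definition of catheter-related infections adopts two tiers. The first is the CDC set: "We will use the definitions by Centre for Disease Control’s (CDC) National Healthcare Safety Network for catheter-related infection (Table 2"; there, UTI requires a positive urine culture. The second is a probable tier in Table 3.

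For probable UTI, Table 3 begins "Patient has at least two of the following signs or symptoms: fever >38.0 °C, suprapubic tenderness" and continues, after AND, with a list of alternatives joined by OR. Most are laboratory findings (dipstick, pyuria, Gram stain, cultures). The list closes with two clinical decisions: a doctor's diagnosis of urinary tract infection, or "doctor starts appropriate antibiotic therapy". A footnote says of frequency, urgency and dysuria that "therefore these cannot be used as symptoms when catheter is in place". Probable CAUTI is then "A probable UTI where an indwelling urinary catheter was in place on the date of event or the 7 days before".

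The Assessments section, which describes how infections are collected after discharge from medical and nursing records, refers to Table 3 only.

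Under Primary and secondary endpoints: "Secondary endpoints are catheter-related infections and other complications, catheter reinsertion rate, use of antibiotics". The De-implementation strategy section addresses physicians and nurses through a local champion, a kick-off meeting with competitive feedback, reminders, and education: "two educational meetings about insertion, care and maintenance of urinary and intravenous catheters will be applied to change HCWs behavior". The Discussion acknowledges that there is no control group.

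**The concern.** An outcome that can be completed by a clinician's decision measures two things: how often infections occur, and how readily clinicians label or treat them. Here those clinicians belong to the staff whom the strategy sets out to influence, and the strategy arrives between the two periods being compared.

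If readiness to diagnose or treat changes at that time, the probable UTI and CAUTI counts change even if no infection is prevented or caused. The segmented regression in the Statistical analysis section adjusts for secular trend, autocorrelation and confounders. A habit change that begins with the intervention has the same timing as a true effect, so without a control series the model would credit it to the strategy.

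At stake are the credibility of any reported reduction in catheter-related infections, and one input to the economic evaluation, which uses catheter-related complications. In addition, an antibiotic start can complete an infection case while antibiotic use is a separate secondary endpoint, so one prescribing shift can move both.

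**Working it through.** The plan states no figure on this point, so there is none to reproduce. The check has three parts.

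**1. What the Table 3 rule accepts.** Let S = at least two qualifying signs or symptoms, L = the first laboratory test listed (dipstick), D = doctor's diagnosis or antibiotic start, with the other laboratory items set aside. Two readings are possible:

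- Natural reading: S AND (L OR D).
- Literal reading, AND binding before OR: (S AND L) OR D.

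| S | L | D | Natural | Literal |
|---|---|---|---|---|
| no | no | no | no case | no case |
| no | no | yes | no case | **case** |
| no | yes | no | no case | no case |
| no | yes | yes | no case | **case** |
| yes | no | no | no case | no case |
| yes | no | yes | **case** | **case** |
| yes | yes | no | case | case |
| yes | yes | yes | case | case |

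In the row S yes, L no, D yes, both readings give a case: the doctor's act replaces all laboratory evidence. The readings differ where S is no and D is yes. There only the literal reading counts a case, without symptoms.

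**2. Which definition is used.** The definitions section adopts Tables 2 and 3. The Assessments section cites Table 3 alone for collection. As written, it is unclear whether Table 2 infections are separately collected and compared, so Table 2 cannot be assumed to act as a safeguard.

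**3. Possible size.** Let f = share of probable UTIs confirmed only by a doctor's decision, and h = relative fall in such labels after the intervention. With no true change in infections:

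apparent rate ratio = 1 − f × h

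The documents give neither f nor h; all values below are assumptions.

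| f | h = 0.25 | h = 0.50 | h = 0.75 |
|---|---|---|---|
| 0.1 | 0.975 | 0.950 | 0.925 |
| 0.3 | 0.925 | 0.850 | 0.775 |
| 0.5 | 0.875 | 0.750 | 0.625 |

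With smaller assumed shifts, f from 0.20 to 0.50 and h from 0.10 to 0.30, the spurious change runs from 0.20 × 0.10 = 2% to 0.50 × 0.30 = 15%. Across all these inputs the range is 2% to 1 − 0.625 = 37.5%. If readiness to label rises, the sign reverses. For scale, the Background cites a 22% CAUTI reduction outside ICUs in a national programme, and a fall from 4 to 0 per 1000 catheter days in the local pilot.

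**The case against.** A reader might infer that a doctor's label alone makes a case. On the natural reading it does not: two signs or symptoms are still needed, against one in Table 2. While a catheter is in place, only fever, suprapubic tenderness and costovertebral angle pain or tenderness count. That is a real gate and it narrows the route. It is not complete, because the probable CAUTI window also covers the 7 days before the event, so the catheter may already be out and the footnote's exclusion no longer applies. The literal reading would remove the gate altogether, which is a reason to add brackets.

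A reader might also infer that the strategy trains doctors in diagnosing or treating UTI. The documents do not say so; the meetings concern insertion, care and maintenance. A habit shift is plausible in staff who are exposed to feedback and reminders about catheters, but it is not documented and could go either way. That doctors know which period they are in follows from the open delivery of the strategy; the article does not state it.

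Three further points stand. The probable tier is labelled as such, and the stricter tier is adopted beside it. The infection endpoint also covers bloodstream infection, vascular infection and phlebitis, and the economic evaluation also uses length of stay, readmission and productivity costs, so a UTI shift is diluted in both. Finally, laboratory results exist only when someone requests a test, so requiring one does not make the count independent of clinicians. This last point argues against simply replacing the main definition, but not against showing the decision-only cases separately.

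Overlap with antibiotic use as an endpoint is not an error in itself; it only means that the two results are not independent evidence.

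**Conclusion.** The point holds in a limited form. Once symptoms are present, a doctor's diagnosis or antibiotic start can supply the whole confirmation of probable UTI, and therefore of probable CAUTI. The missing brackets leave even the symptom requirement open to dispute. The collection text names only this tier. In a before-after design without a control, a change in labelling or prescribing that coincides with the strategy cannot be separated from a true reduction in this tier.

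Size and direction cannot be derived from the documents. The 2% to 37.5% range only illustrates assumed inputs, applies to probable UTI and not to all infections, and is not an estimate of bias. The documents do not support a claim that the infection result will be biased. The primary endpoint, which concerns inappropriate indications, does not use this definition. This is a minor, inexpensive improvement to a secondary endpoint.

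**What to change.** - Bracket the probable UTI definition in Table 3 as symptoms AND (any one of the listed items).
- Reconcile the definitions section with the Assessments section, so that Table 2 infections are collected and compared between periods in their own right.
- For each Table 3 case, record which item confirmed it. A low-count culture under antibiotic treatment counts as a laboratory item for this purpose.
- Report the before-after comparison of probable UTI and probable CAUTI twice: with all cases, and without those confirmed only by a doctor's diagnosis or antibiotic start. Tabulate the decision-only cases by period, so that a shift in them is visible.

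The cost is one flag per case, an extra table row, and fewer events, hence less precision, in the restricted analysis. Laboratory items still depend on test ordering, so this reduces the bias without removing it. Nothing in patient care changes.
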